## Abstract

**Background:**

Urinary incontinence is highly prevalent in women while pelvic floor muscle training is recommended as the first-line therapy. However, the exact treatment regimen is poorly understood. Also, patients with pelvic floor muscle damage may have decreased muscle proprioception and cannot contract their muscles properly. Other conservative treatments including electromagnetic stimulation are suggested by several guidelines. Thus, the present study aims to compare the effectiveness of electromagnetic stimulation combined with pelvic floor muscle training as a conjunct treatment for urinary incontinence and different treatment frequencies will be investigated.

**Methods/design:**

This is a randomized, controlled clinical trial. We will include 165 patients with urinary incontinence from the outpatient center. Participants who meet the inclusion criteria will be randomly allocated to three groups: the pelvic floor muscle training group (active control group), the low-frequency electromagnetic stimulation group (group 1), and the high-frequency electromagnetic stimulation group (group 2). Both group 1 and group 2 will receive ten sessions of electromagnetic stimulation. Group 1 will be treated twice per week for 5 weeks while group 2 will receive 10 days of continuous treatment. The primary outcome is the change in International Consultation on Incontinence Questionnaire–Short Form cores after the ten sessions of the treatment, while the secondary outcomes include a 3-day bladder diary, pelvic floor muscle function, pelvic organ prolapse quantification, and quality of life assessed by SF-12. All the measurements will be assessed at baseline, after the intervention, and after 3 months of follow-up.

**Discussion:**

The present trial is designed to investigate the effects of a conjunct physiotherapy program for urinary incontinence in women. We hypothesize that this strategy is more effective than pelvic floor muscle training alone, and high-frequency electromagnetic stimulation will be superior to the low-frequency magnetic stimulation group.

**Supplementary Information:**

The online version contains supplementary material available at 10.1186/s13063-024-08103-y.

## Administrative information

Note: The numbers in curly brackets in this protocol refer to the SPIRIT checklist item numbers. The order of the items has been modified to group similar items (see https://www.equator-network.org/reporting-guidelines/spirit-2013-statement-defining-standard-protocol-items-for-clinical-trials/).

## Introduction

### Background and rationale {6a}

Urinary incontinence (UI) is a highly prevalent health issue globally. UI is described as involuntary leakage of urine, and it happens in both sexes but is more commonly seen in women [2]. The risk factors of UI in women are usually associated with impaired bladder and pelvic floor muscle function, and such conditions usually arise with pregnancy and menopause. The prevalence of UI gradually increases with aging. Around 6.9% of women between 20 and 39 years old suffer from UI, increasing to 31.7% in women aged above 80 [3, 4]. Based on the criteria of the International Continence Society (ICS) and the International Urogynecological Association (IUGA), there are two main subtypes of UI: urgency urinary incontinence (UUI) and stress urinary incontinence (SUI) [2]. SUI is usually associated with an increase in intra-abdominal pressure, while UUI is often associated with a sudden desire to void that is usually difficult to defer [5]. Mixed urinary incontinence (MUI) is a condition when the two subtypes coexist. Since UI could lead to limited physical activity, damaged sexual function, and other psychological problems, it is detrimental to the patient’s psychosocial well-being and quality of life [6].

Pelvic floor muscle training (PFMT) is regarded as the first-line therapy for UI in terms of a wide range of spectrums, including treatment response, quality of life (QoL), the volume of urine leakage, and treatment satisfaction [7]. PFMT could improve the stability of the urethra. A single bout of pelvic floor muscle contraction can narrow the levator hiatus area, increase the urethral closer pressure, and lift the rectum and bladder, thus reducing the symptoms of UI [8]. However, most of the comparisons with other active treatments were made in small, single-center trials, making it difficult to draw the conclusion of whether PFMT is superior to other treatments such as electromagnetic stimulation or vaginal cones [9]. Also, it is unclear whether combining PFMT with these treatments could have additional benefits.

Recent studies have attempted to investigate the different treatment strategies to maximize the efficacy of PFMT, including non-invasive electrical stimulation, biofeedback, and extracorporeal magnetic stimulation for lower urinary tract symptoms in women [10–13]. Electrical stimulation applies an intravaginal probe or surface electrodes that do not penetrate the skin, while magnetic stimulation utilizes a magnetic coil to generate an eddy current in the target tissue to trigger muscle contraction. Both of the two are passive muscle training. Biofeedback is defined as verbal or visual feedback to the participants to help with muscle contraction and relaxation, especially for patients with pelvic muscle damage who cannot contract them correctly [7]. These strategies are becoming important components of treatment modules and routine care for patients with UI. According to Chinese clinical settings, electrical stimulation and magnetic stimulation are usually combined as an adjunct treatment to assist PFMT. However, a consensus on the treatment regimen has not been achieved, such as treatment frequency.

### Objectives {7}

The first aim of the present study is to investigate the efficacy and safety of combining electromagnetic stimulation with PFMT for patients with UI. The second aim is to delineate the optimal treatment frequency of this strategy.

### Trial design {8}

This trial is a randomized controlled trial with a post-intervention follow-up of 3 months. Participants who meet the inclusion criteria will be included in the study. All the participants will be randomly allocated to the intervention and control groups in a 1:1:1 ratio using a randomization sequence.

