## Methods: participants, interventions, and outcomes

### Study setting {9}

The three groups are the active control group: PFMT, twice per week for 5 weeks; group 1 (low-frequency magnetic stimulation group): PFMT + electromagnetic stimulation, twice per week for 5 weeks, every two sessions will be separated by at least 48 h; group 2 (high-frequency magnetic stimulation group): PFMT + electromagnetic stimulation, continuous treatment for 10 days. All the patients will also receive a 3-month post-intervention follow-up. The randomization process will be conducted by an online random number generator. The random numbers will be kept in opaque envelopes. Then, a research assistant will allocate the numbers to the participants according to the order of inclusion. The present study cannot blind the practitioner and the participants due to the nature of the interventions. However, the outcome assessor and data analyst will be blinded.

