#### Sample size {14}

The present study intends to apply ICIQ-SF as the primary outcome. After calculation, a sample size of 44 in each group is able to provide 80% power to detect a within-between-group difference measured using ICIQ-SF at three time points, assuming a small effect size (Cohen’s *f*) of 0.125 and a two-sided significance level of 5%. Considering that there is a 20% dropout rate, the study will increase the sample size to 165 in total.

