### Assignment of interventions: allocation

#### Sequence generation {16a}

After confirming the consent, statistical program R will be applied to generate a randomization sequence. The allocation will be carried out by a research assistant who has no role in delivering the intervention and the data analysis. All the participants will be allocated in a 1:1:1 ratio.

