## Discussion

The first aim of this randomized controlled trial is to provide a comprehensive physiotherapy program that combines PFMT and electromagnetic stimulation adapted to the needs of women with UI. The anticipated results of this trial could be incorporated into routine clinical practice and offer an effective strategy to improve symptoms of UI and their general well-being. It will also recommend a suitable and standardized protocol that consists of different conservative interventions for patients with UI.

As previously mentioned, PFMT is recommended as the first-line therapy for patients with lower urinary tract symptoms [7]. However, a number of issues do exist when considering providing PFMT for UI patients. In China, it is difficult to provide one-on-one supervised PFMT for patients due to the heavy workload of healthcare providers and the number of patients. Compared with individualized PFMT, group-based PFMT, while having a similar effect [14], is still difficult to generalize to a large population. The primary reason is that it is difficult to make appointments with multiple patients at the same time in Chinese clinical settings, and the patient’s subjective perception and rehabilitation needs cannot be met. According to two Cochrane reviews, electrical stimulation could improve symptoms of lower urinary tract symptoms, such as overactive bladder and stress UI [37, 38]. However, previous studies should also be interpreted with caution since some of the studies were deemed to have a relatively high risk of bias including baseline differences between the groups and small sample sizes. Also, the mode and the type of delivery of such interventions remain controversial and poorly standardized (e.g., intervention frequency) as suggested by the European Association of Urology (EAU)’ guideline [39]. Based on the above research status, the present study is the first to explore the effectiveness of high-frequency versus low-frequency electromagnetic stimulation in the treatment of UI. Thus, one of the strengths of the present study is that the conjunct effect of PFMT and electromagnetic simulation can be evaluated with rigorous quality control, and a standardized intervention frequency can be established. Another strength of the study is that both patients’ subjective data and objective data will be collected for a comprehensive analysis of their symptoms and the impact on their quality of life.

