There are several limitations of the current trial. Firstly, it is difficult to keep the participants blinded to the intervention due to the nature of electromagnetic stimulation and PFMT. The researchers will explain the details of the study carefully and inform the participants about the benefits of different interventions. Secondly, the age of the participants ranges from 18 to 75, which is heterogeneous and UI types should be different. We will consider subgroup analysis that may include different age groups and UI types when conducting the research.

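### No strata or blocks are stated for allocation, and the GEE states no adjustment for UI type or baseline severity, factors the protocol itself treats as mattering

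*Protocol article*

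**What the plan says.** **Allocation.** Trial design {8} gives only the ratio and a sequence: "All the participants will be randomly allocated to the intervention and control groups in a 1:1:1 ratio using a randomization sequence". Study setting {9} adds: "The randomization process will be conducted by an online random number generator". The numbers go into opaque envelopes and are assigned in order of inclusion. Sequence generation {16a} states that "statistical program R will be applied to generate a randomization sequence", again at 1:1:1. Concealment mechanism {16b} and Implementation {16c} cover who holds the list and when the arm is revealed. None of the five sections names a block, a stratum or minimisation.

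**Factors that matter.** The Discussion says the age range is one "which is heterogeneous and UI types should be different", and describes part of the earlier literature as having "high risk of bias including baseline differences between the groups and small sample sizes". Statistical methods {20a} expects age, BMI and UI severity to influence outcomes and cuts severity at an ICIQ-SF of 13. The consent section {26a} uses the QUID to establish UI type as stress or mixed before enrolment.

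**Analysis.** Statistical methods {20a} compares baseline data by significance tests and analyses outcomes with GEE models. It states no covariate for UI type or baseline severity.

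**The concern.** The primary outcome is change in ICIQ-SF, and UI type and baseline severity plausibly bear on how far that score can move. With about 55 women per arm, simple allocation can leave visible differences on such factors between arms. Two hypotheses depend on comparisons among three arms (combined treatment against pelvic floor training alone, and high against low frequency), so an imbalance in any arm touches at least one of them.

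The stake is precision and how convincing the result looks. A reader who sees arms differing by 15 points in mixed UI could make the same complaint that the Discussion makes about earlier trials. Baseline significance tests do not help: they describe an imbalance without removing its effect on the estimate.

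**Working it through.** **1. The plan's own figure.** Sample size {14} states that "a sample size of 44 in each group is able to provide 80% power", with an effect size f "of 0.125 and a two-sided significance level of 5" percent, for a "difference measured using ICIQ-SF at three time points". For a repeated-measures within-between interaction:

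- λ = f²·N·m/(1−ρ), with N = 132, m = 3 and ρ = 0.5 (assumed; none is stated)
- λ = 0.015625 × 132 × 3 / 0.5 = 12.375
- df = (3−1)(3−1) = 4 and (132−3)(3−1) = 258
- Power = 0.808; with 43 per arm it is 0.797

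So 44 per arm is the minimum, and 132/0.8 = 165, or 55 per arm. The stated size reproduces, so arms of 55 are the right basis for the next step.

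**2. Inputs for the imbalance check.** n = 55 per arm comes from the plan. The prevalence p of the factor (mixed UI, say, or ICIQ-SF ≥13) is not given, so it is assumed and varied. The 15-point gap is a working threshold, not a figure from the plan.

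**3. One given pair of arms.** By normal approximation, SE = √(2p(1−p)/n). At p = 0.5 this is √(0.5/55) = 0.0953, so z = 0.15/0.0953 = 1.57 and P ≈ 0.116. The exact binomial value is 0.105. It is lower because 15 points of 55 is 8.25 women, so the gap must be at least 9.

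**4. Any of the three pairs.** This is one minus the probability that all three pairs stay within 15 points, enumerated over three binomials for fixed arms and simulated for simple randomisation of 165 women.

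| Prevalence (assumed) | One given pair, 55 per arm | Any pair, 55 per arm | Any pair, simple randomisation |
|---|---|---|---|
| 20% | 4.2% | 10.4% | 12% |
| 30% | 7.6% | 17.9% | 20% |
| 40% | 9.8% | 22.2% | 25% |
| 50% | 10.5% | 23.6% | 26% |

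At 10% prevalence the any-pair figure with 55 per arm is 1.9%. For one given pair under simple randomisation the chance is 8.8% at 30% prevalence and 11.8% at 50%.

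**5. With stratified blocks.** In simulated permuted blocks of 6 within four strata (two binary factors), a gap of 15 points or more on either factor occurred in 0 of 4,000 trials, at prevalences of 50%/50% and again at 30%/50%.

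**The case against.** **The article is silent on restriction; it does not rule it out.** A reader might infer that allocation is declared to be unrestricted. The text does not say so. A blocked list is also handed out in order of inclusion, block sizes are often kept out of public papers, and a fuller protocol may hold them. This stands: the supportable statement is that no strata or blocks are stated, and the figures above are conditional on simple allocation.

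**Arm sizes.** A reader might go on to argue that plain random numbers leave the smallest arm below 44 in about 8% of trials and so threaten power. That assumes independent draws, whereas the stated 1:1:1 ratio fits a fixed-size list equally well. Even arms of 44, 60 and 61 have a harmonic mean of 3/(1/44 + 1/60 + 1/61) = 53.8 against 55, a loss of about 2%. This is not part of the point.

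**One in four.** It is tempting to quote this as the chance of imbalance on UI type or severity. It holds only for one factor, any pair and a prevalence of about 40–50%. For either of two independent factors with 55 per arm it would be 1 − (1 − 0.179)² = 33% at 30% prevalence and 1 − (1 − 0.236)² = 42% at 50%. For one given pair on one factor it is near one in ten.

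**Validity and severity.** Simple randomisation is unbiased, and its type I error already allows for chance imbalance. The Discussion's remark on heterogeneity concerns age and UI type; severity appears only in Statistical methods {20a}. Baseline ICIQ-SF is one of the three time points and the outcome is change, so severity is partly accounted for already. All of this stands. It narrows the harm to precision and credibility and leaves UI type as the factor with no stated handling at all.

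**Adjustment detail belongs in an SAP.** That is fair, so the lack of covariates is not called an error here. The model is simply the cheapest place to deal with the matter.

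**Conclusion.** The point holds as an improvement worth making. No strata or blocks are stated in any allocation section, and no adjustment for UI type or baseline severity is stated, although the protocol treats these as relevant and criticises earlier trials for baseline differences.

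If allocation is simple, a given binary factor will differ by 15 points or more between some two arms in roughly one trial in four or five. That rests on an assumed prevalence of 30–50%; at 20% it falls to about one in eight to ten. For any single planned comparison it is near one in ten. The 15-point threshold has not been translated into ICIQ-SF points, so these figures measure imbalance and not an error in the treatment effect. The documents do not support a claim of bias, of inflated type I error or of an underpowered design.

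**What to change.** **Analysis, useful at any stage.** In the primary GEE, model the post-baseline ICIQ-SF with baseline ICIQ-SF as a continuous covariate and QUID type (stress/mixed) as a factor. Fix this before the analyst sees outcomes by arm. Both variables are already collected, so the cost is a sentence of text.

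**Allocation, only for women not yet randomised.** Generate the R sequence in permuted blocks of randomly varying size (for example 3, 6 and 9), concealed from recruiting staff and stratified by UI type and ICIQ-SF <13/≥13. The ICIQ-SF must be scored before allocation. Two binary factors give four strata, so the envelope system would need four series.

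The Trial status section puts recruitment from July 2022 to June 2023, so this is an amendment during recruitment. Blocks also make allocation slightly more predictable in an open trial; varying the block size limits this. If allocation is already complete, only the covariate adjustment and a plain report of the method actually used remain.

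**Text.** State in Sequence generation {16a} whether allocation is simple, blocked or stratified. If blocks or strata already exist in a fuller protocol, saying so settles the allocation part.

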## Methods: participants, interventions, and outcomes

### Study setting {9}

The three groups are the active control group: PFMT, twice per week for 5 weeks; group 1 (low-frequency magnetic stimulation group): PFMT + electromagnetic stimulation, twice per week for 5 weeks, every two sessions will be separated by at least 48 h; group 2 (high-frequency magnetic stimulation group): PFMT + electromagnetic stimulation, continuous treatment for 10 days. All the patients will also receive a 3-month post-intervention follow-up. The randomization process will be conducted by an online random number generator. The random numbers will be kept in opaque envelopes. Then, a research assistant will allocate the numbers to the participants according to the order of inclusion. The present study cannot blind the practitioner and the participants due to the nature of the interventions. However, the outcome assessor and data analyst will be blinded.

### Eligibility criteria [1]

The following are the inclusion criteria:Women aged 18–75 years.Women who report at least three episodes of involuntary urine leakage weekly during the preceding 3 months [14].Types of UI will be confirmed by the Questionnaire for Incontinence Diagnosis [15].

The following are the exclusion criteria:Body mass index ≥ 35 (equals weight in kilograms divided by height in meters squared)Restricted body movementPelvic Organ Prolapse Quantification System >  stage 2History of pelvic surgery or physiotherapyUse of medication for UI or affects skeletal muscle functionHistory of electromagnetic stimulation therapy for UINeurological diseasesPregnancyMetal implants in the body, such as a pacemakerOther risk factors or comorbidities that interfere with the study

### Who will take informed consent? {26a}

Female patients aged from 18 to 75 who report weekly involuntary urine loss of three or more episodes for the past 3 months will be included, such criteria have been used widely in previous RCTs on UI [14]. Then, the validated Questionnaire for Incontinence Diagnosis (QUID) will be applied to confirm the type of UI as a pattern of stress/mixed UI. The eligible participants will be provided written informed consent with information illustrating the purpose and the detailed procedures of the present study after they meet the eligibility criteria. The consent will be obtained by the obstetricians and will be kept confidential and aimed only at research purposes. Data collected will be stored in a locker at the principal investigator’s office, and an electronic version will be protected by a password on the hospital computer.

### Additional consent provisions for collection and use of participant data and biological specimens {26b}

No biological specimens will be collected from this study. If additional data or biological specimens are required, they must be authorized by ethical boards and be included in the consent.

### Interventions

#### Rationale for the choice of comparators {6b}

The participants in the active control group will receive PFMT, which is recommended as the first-line therapy for UI [7]. Patients with UI are usually informed to do PFMT at home or under supervision by physiotherapists.

#### Intervention description {11a}

All the participants in the three groups will receive PFMT. The efficacy of PFMT has been reported widely in improving or curing UI in all age groups [16]. The International Continence Society published the guideline on managing incontinence and suggests that supervised PFMT should be considered as the first-line treatment for stress and mixed UI in women [17]. Due to the consideration of manpower and financial resources, the evidence from the GROUP study showed that the group-based PFMT can also demonstrate similar effects for the treatment of UI when compared with supervised individual PFMT [14]. To maximize the effect of PFMT and the patient’s adherence, the psychological self-determination theory (SDT) will be embedded in this treatment program [18]. SDT has been widely adopted in the literature on exercise behavior, and it assumes that all humans possess three psychological needs: a need for autonomy, a need for relatedness, and a need for competence [19]. Rationale of the PFMT will be provided for the patients, as well as clear goals with feedback and interpersonal interaction. All the abovementioned SDT strategies have no direct effect on UI.

Each electromagnetic stimulation session consists of 10-min electrical and 20-min magnetic stimulation. Electrical and magnetic stimulation devices (B4P electrical stimulator and MTS magnetic stimulator, Nanjing Medlander Medical Technology Co., Ltd.) will be applied for delivering the intervention. Details of the intervention are illustrated below (Table 1). All the uro-physiotherapists will be trained before the initiation of the study to ensure the delivery of a standardized treatment procedure. The standardized procedure includes the delivery of PFMT and the manipulation of the electrical and magnetic stimulation device.

**Table 1 Tab1:** Standardization of training and protocols

Group	Standardized training program	Detailed dosage	Time in total
Active control group	Sustained contractions	Patients complete PFMT by themselves, 6–10 s for each contraction, and every two contractions are separated by a period of 10-s rest; 8–10 reps per set for 1–2 sets	50 min
	Phasic contractions	The patient completes pelvic floor muscle contractions of 2–5 s each, followed by rest intervals of 4–10 s. Each set contains 10 contractions, 1–3 sets each	
	Training guidance	Under the guidance of the instructor, patients perform PFMT, combined with breathing and relaxation training	
Group 1	PFMT + + electromagnetic stimulation	PFMT is the same as the active control group Electrical stimulation: 20–60 Hz, the pulse width of 200–600 μs, 10 min of stimulation Magnetic stimulation: 15 Hz for 2 s and 30 Hz for 3s, with a rest interval of 5 s, 20 min of intervention Twice per week for 5 weeks	
Group 2	PFMT + + electromagnetic stimulation	PFMT is the same as the active control group Electrical stimulation: 20–60 Hz, the pulse width of 200–600 μs, 10 min of stimulation Magnetic stimulation: 15 Hz for 2 s and 30 Hz for 3 s, with a rest interval of 5 s, 20 min of intervention 10 consecutive days	50min

